## **Dissemination of results and publication policy**

Dissemination of the results will be carried out at different levels in order to maximize the impact of the study and benefit the community, participants and public policy makers.

- Scientific dissemination: The results of the study will be published in high impact scientific journals in the field of music therapy and psychiatry, such as PLOS ONE or similar open access journals, to ensure accessibility of the findings to researchers and clinicians.
- Dissemination to the community: These will be planned with the clinical staff of the institution. These meetings will allow socializing the findings and answering questions, promoting a better understanding of the potential benefits of music therapy.
- Dissemination to policy makers: If the findings suggest significant benefits, executive summaries will be generated and presentations will be made to local and national agencies responsible for mental health policy. The intention is to provide evidence to support the inclusion of music therapy in mental health programs.

## **Publication Policy**

To ensure clarity and transparency in the publication of results, the following guidelines will be established:

- Responsibility for publication: The research team will take the lead in the publication of findings. Decisions regarding the choice of journals and content of manuscripts will be made in consensus by the research team.
- Acknowledgement of contributions: All investigators and collaborators who have contributed substantially to the design, development, analysis, or interpretation of data will be acknowledged in publications, following international standards for authorship attribution and acknowledgement of contributions. In addition, the institutions and individuals who provided resources or supported the study will be mentioned and thanked.
- Access to the results: It will be guaranteed that the publications resulting from the study will be open access, in order to promote the wide availability of the knowledge generated, in line with the commitment to transparency and community benefit.

The recruitment process will involve a convenience sample of patients hospitalized at Clínica Montserrat who meet the inclusion and exclusion criteria over a projected period of forty-two days. Given that the average hospitalization duration is approximately ten days, the recruitment schedule is organized to allow each participant to access the intervention prior to their anticipated discharge.

Daily recruitment will begin with a review of the patient census, listing each patient's hospitalization days. This review will identify eligible patients for recruitment each day based on their hospitalization timeline. Selected patients will be prioritized, starting with those furthest along in their hospitalization (ideally those on their ninth day) and continuing with those who have fewer days, ensuring they meet the criteria to receive the intervention in a timely manner.

On each recruitment day, eligible patients will be actively sought within the clinic to provide them with information about the study and obtain informed consent from those willing to participate. Daily recruitment will yield a count of recruited patients and a record of those who decline, to adjust the next day's recruitment targets accordingly.

Priority will initially be given to patients with longer hospitalization durations to maximize intervention exposure. As recruitment progresses and patients with extended stays are enrolled, focus will gradually shift toward those with shorter hospitalizations. This approach is designed to maintain consistent group sizes for the intervention sessions, facilitating robust and enriched group therapy sessions throughout the recruitment period.

This systematic and phased recruitment strategy is intended to ensure timely enrollment and intervention exposure for each participant while adhering to the study's target sample size and optimizing group therapy dynamics.

[figure not shown]

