**Variables**

Sociodemographic data will be collected, including age, gender, educational level, and clinical information such as hospitalization diagnosis, levels of anxiety, depression, stress, general discomfort, life satisfaction perception, intervention-related data like expectations regarding music therapy, and the weekly intensity of music therapy received.

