## **Data Management and Statistical Analysis**

The sample size will be calculated with a power of 85% and a bilateral significance level of 0.05, aiming to detect a mean difference of 4 between experimental and control groups, with an estimated standard deviation of 5. A minimum sample size of 60 subjects (30 per group) will be targeted, with 35 per group to account for possible dropouts.

Data analysis will use Jamovi software, version 2.6 (2024). Descriptive analysis will characterize the sample, including central tendency and dispersion measures, and the normality of continuous variables will be assessed using the Shapiro-Wilk test. Differences between intervention and control groups will be determined using the Mann-Whitney U test for non-normally distributed data, and correlation analyses will use Spearman's nonparametric test where applicable. The analysis will include evaluations of sociodemographic and initial characterization variables, complemented by a correlation matrix for primary variables and outcomes.

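### Hospital day at entry governs eligibility but is not a listed variable, and the only between-arm test named adjusts for no baseline value: a probably small loss of precision, not bias

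*Protocol*

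**What the plan says.** **Recruitment.** The recruitment text (Protocol, placed under Publication Policy) describes a daily census review that lists each patient's days in hospital: "This review will identify eligible patients for recruitment each day based on their hospitalization timeline". Patients furthest along in their stay are approached first, ideally on day nine, and as recruitment goes on "focus will gradually shift toward those with shorter hospitalizations". The Randomization section gives a different rule for whom to approach: a random daily draw.

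**Eligibility.** Both sets of criteria use length of stay. The Participants section requires at least 48 hours in hospital at recruitment; the Population and Sample section requires less than 48 hours. Both exclude stays over six days, one counted at selection and the other before the first session.

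**Variables.** The Variables section lists age, gender, education and "clinical information such as hospitalization diagnosis, levels of anxiety, depression, stress, general discomfort, life satisfaction perception", plus items on expectations and on the intensity received. The Clinical Variables list has diagnosis and symptom severity. Hospital day at entry is in none of these lists.

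**Allocation and analysis.** Allocation is a random number cut at 0.5 for each record, with no blocks or strata. Data Management and Statistical Analysis names one between-arm method: "Differences between intervention and control groups will be determined using the Mann-Whitney U test for non-normally distributed data". Baseline variables otherwise appear only in descriptive and correlation analyses.

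**The concern.** By the protocol's own account, stays average about ten days, every patient has had medication adjusted in the past two weeks, and the study intervention takes one week. Patients may therefore start that week at different stages of a short, actively treated admission. If symptoms change with time since admission, part of the spread in the outcome comes from stage of stay, and an unadjusted test leaves that part in the error term. Baseline DASS-21 measures how severe symptoms are, not how far into the stay the patient is, so it may not capture all of this.

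At stake is some precision in the high- versus low-frequency comparison. The description of the sample is also affected: if the entry day is not recorded as study data, the report cannot show at what stage patients entered or whether the arms were alike. The specific objective of relating clinical characteristics to response could not use it either.

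**Working it through.** **1. The plan's own sample size.** Data Management and Statistical Analysis gives the inputs: two-sided 5% significance, 85% power, a target difference of 4 points between the arms, and an SD of 5.

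- Normal approximation: n per arm = 2 × 5² × (1.960 + 1.036)² / 4² = 28.1, rounded up to 29.
- Exact noncentral t: power is 84.9% at 29 per arm and 86.1% at 30, so 30 per arm is needed.
- Dropout: 30/35 = 0.857, an allowance of 14.3%.

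This reproduces "A minimum sample size of 60 subjects (30 per group) will be targeted, with 35 per group to account for possible dropouts". The sample size is sound on its own inputs, and the unadjusted plan already exceeds 85% power.

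**2. What adjustment for hospital day alone would add.** The protocol gives no relation between hospital day and outcome. Assumptions: 30 per arm, total SD 5, entry days spread evenly, outcome changing by b = 0.5 to 1 point per hospital day.

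- SD of entry day over k equally likely days = √((k² − 1)/12)
- Share of variance R² = (b × SD of day / 5)²
- Residual SD = 5 × √(1 − R²), put into the noncentral t power for a difference of 4

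| Entry window assumed | SD of day | R² | Residual SD | Power at 30 per arm |
|---|---|---|---|---|
| No adjustment | – | 0 | 5 | 86.1% |
| Days 1-2 (under 48 hours) | 0.50 | 0.25-1% | 4.99-4.97 | 86.2-86.5% |
| Days 2-6 (at least 48 hours, not over six days) | 1.41 | 2-8% | 4.95-4.80 | 86.8-88.8% |

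The upper slope is generous: 1 point per day over days 2 to 6 is a 4-point gradient, as large as the difference the trial is planned to detect.

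**3. Chance imbalance between the arms, days 2-6.** The standard error of the difference in mean entry day is 1.41 × √(2/30) = 0.37 day, so the 95% range is ±0.72 day. At 0.5 to 1 point per day this is worth 0.4 to 0.7 points. It is not an additional error. The unadjusted treatment difference has a standard error of 5 × √(2/30) = 1.29 points (95% about ±2.6), which already includes it.

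**4. What remains once baseline DASS-21 is in the model.** The protocol gives no correlation of baseline with outcome, so take 0.5 as an assumption. Residual SD is 5 × √(1 − 0.25) = 4.33, and power is 94.0%. If hospital day then explained a full 2 to 8% of the remaining variance, power would be 94.4 to 95.6%. Any overlap between hospital day and baseline severity makes that less. Under this assumption most of the gain comes from the baseline score.

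**The case against.** The strongest reply is that choosing covariates is usual SAP business, that the variable list is open-ended, that the census already holds the hospital day, and that the plan meets its power target anyway. Much of this stands. The absence of a covariate list is not the fault here, and the power target is met. What an unseen SAP does not undo is that the protocol fixes its data items without this one and names a single between-arm test that takes no covariate. The test is named only for non-normal data; the method for the other case is left open.

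Four stronger readings are tempting, and the protocol supports none of them.

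- *The drift from long to short stays biases the comparison.* It does not. Allocation is random whatever the hospital day, so the drift applies to both arms alike.
- *Entry runs from day 2 to day 9, and the loss is large.* With the same slopes that window would give R² of 5 to 21% and power of 88 to 93%. It conflicts with the six-day exclusion, and the recruitment text itself is limited to patients who meet the criteria. Those figures should not be relied on.
- *Hospital day alone decides who is approached.* The Randomization section describes a random draw instead. What holds under either text is that hospital day governs eligibility.
- *Leaving the variable off the list means it will be unavailable.* The census has it. It is simply not made study data.

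**Conclusion.** The point holds as a modest matter of precision. Hospital day governs eligibility and, in the recruitment text, the order of approach. It is not a listed variable, is not balanced by the allocation, and cannot enter the one test that is named. On entry over days 2 to 6 and an assumed 0.5 to 1 point per day, adjustment recovers 2 to 8% of variance, about 1 to 3 percentage points of power. It recovers less beside baseline DASS-21 and almost nothing if entry is under 48 hours. The slope, the even spread of entry days and the baseline correlation are all assumptions. The protocol also does not say which DASS-21 scale the difference of 4 and SD of 5 refer to. The case for acting is that the change costs very little and that a covariate named in advance avoids a post hoc choice if the arms happen to differ. The more useful part of the change is the adjustment for baseline DASS-21.

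**What to change.** 1. Add hospital day at the baseline assessment, copied from the daily census, to the Variables and Clinical Variables lists, and show it by arm in the baseline table.
2. In Data Management and Statistical Analysis, replace the unadjusted between-arm comparison with a pre-specified ANCOVA of post-intervention DASS-21 on arm, with baseline DASS-21 as the main covariate and hospital day as the second. Name a rank ANCOVA for the non-normal case.
3. Reconcile the passages that set the range of this covariate: at least versus less than 48 hours, the six-day exclusion versus approach ideally on day nine, and the random daily draw versus longest stay first.

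The cost is one data column from a list the team already reads, one row in a table, and one more model term. The downside is that the named test changes: the Mann-Whitney test has no place for a covariate, so this is a replacement and not an addition. The power figures above are for a t test or ANCOVA, not for the rank test. No extra patients, visits or staff are needed.

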## Problems anticipated

The use of self-reports and observation by the music therapist may generate biases of social desirability and subjectivity, affecting the validity of the results. Although validated scales such as the DASS-21 and the global life satisfaction scale are used, the CISMA scale is still under development, limiting the robustness of the measurements. The absence of a blinded control group could also introduce expectation bias, especially in those receiving a less intensive intervention. Additionally, the low diversity of psychiatric diagnoses limits the generalizability of the results. It is suggested that future research include additional objective measures and a more diverse sample to strengthen the validity and applicability of these findings.

## Ethics

The present work was governed by the biomedical research recommendations of the Declaration of Helsinki of the World Medical Association, as well as the related regulations in the Colombian legislation in force according to Resolution 8430 of 1993 (Technical and administrative scientific norms for health research) (Ministry of Health, 1 1993). On the other hand, according to Resolution No. 008430 OF 1993 (OCTOBER 4, 1993) of the Ministry of Health, this research was considered to be of minimal risk due to the application of common procedures (psychological examinations) to the selected sample. The procedures in the research were carried out by qualified and competent professionals in this type of intervention from a clinical perspective, the researchers did not face conflicts of interest.

The principle of autonomy of the individual to whom participation in the study was proposed was respected, because the decision to participate was free and voluntary and there was no involvement in the treatment by the decision not to participate. For the inclusion of a patient in the study, it was mandatory that he/she did so voluntarily and after signing the informed consent, after receiving detailed information about the study and clarification of any doubts by the qualified professional.

The privacy and confidentiality of the data was guaranteed by assigning an identification code in the research records, likewise, the process of anonymization of sensitive data defined in Law 1581 of 2012 was carried out if necessary. Likewise, security measures were established to protect the information collected in the virtual storage platform of google sheets, With limited access to researchers' own emails which allowed limiting access to the database only to the team of researchers and the collection center (Clínica Montserrat). The results were processed with the assigned codes, and at the time of the disclosure of results, it was done in a general way, without identifying any of the participants. The results of the evaluations could be explained to the participants, if they so wished, privately at the end of the study.

To guarantee the principle of beneficence, although no direct individual benefit was given to the participants, in addition to further follow-up on the significant symptoms of their underlying affective pathology, it highlighted the social and scientific value of

the research in terms of contributing to knowledge about characteristics that impacted the patients' response to music therapy.

To ensure nonmaleficence, the investigators who applied the tests took into account the immediate suspension of the study when they noticed any risk or harm to the health of the participating subjects, or discontinued on an individual basis when they noticed a particular risk in a research subject.

**Informed consent forms**

- Appendix below

**2. Materials and Supplies**

These expenses cover the materials necessary to conduct interventions and data collection activities.

| Material/Supply                               | Justification                    | Unit Cost   | Quantity | Subtotal    |
|-----------------------------------------------|----------------------------------|-------------|----------|-------------|
| MIDI Device Rental                            | Creative MT interventions        | \$600,000   | 1        | \$600,000   |
| Piano and Organet Rental                      | Conducting directed MT sessions  | \$1,200,000 | 1        | \$1,200,000 |
| Subscription to Bibliographic Databases (UEB) | Access to international sources  | \$1,500,000 | 1        | \$1,500,000 |
| Access to ICSN Bibliographic Material         | Key scientific literature access | \$1,000,000 | 1        | \$1,000,000 |
| Total                                         |                                  |             |          | \$4,300,000 |

**Justification:** The subscription to bibliographic resources and rental of instruments are essential for carrying out and enhancing music therapy interventions, ensuring a high-quality, evidence-backed approach.

### 3. Publication Costs

The budget includes costs associated with publishing results in an indexed scientific journal, crucial for the dissemination and validation of the project's findings.

| Publication                    | Justification                | Unit Cost (USD) | Exchange Rate | Subtotal    |
|--------------------------------|------------------------------|-----------------|---------------|-------------|
| Publication in Indexed Journal | Editorial publication rights | \$800           | \$3,900       | \$3,120,000 |
| Total                          |                              |                 |               | \$3,120,000 |

**Justification:** Publishing in a high-impact scientific journal ensures the dissemination of knowledge generated by the project, contributing to the fields of music therapy and mental health.

### Overall Project Budget Summary

| Item                   | Total Cost   |
|------------------------|--------------|
| Personnel Costs        | \$22,417,360 |
| Materials and Supplies | \$4,300,000  |
| Publication            | \$3,120,000  |
| Total Project Cost     | \$29,837,360 |

### Other support for the project

- Self-funded

## **Collaboration with other scientists or research institutions**

- Instituto Colombiano del Sistema Nervioso-Clínica Montserrat
- Universidad El Bosque

## **Links to other projects**

- Does not Apply.

## **Curriculum Vitae of investigators**

- Appendix below

## **Other research activities of the investigators**

The principal investigator of this study does not participate in other research projects at present, which guarantees that he devotes his time and attention exclusively to the supervision and development of this study. This exclusive dedication allows us to maintain high quality standards and detailed monitoring of compliance with the objectives and procedures established in the protocol.

In addition, this study has been financed entirely self-funded. This ensures that there are no conflicts of interest with external entities and that the decisions in the development of the research are oriented exclusively to the fulfillment of the scientific and ethical objectives of the project, without the influence of sponsors or third party financing.

The absence of other research commitments and the self-funded nature of this study contribute to the independence, impartiality in the execution and analysis of the results, strengthening the validity and reliability of the study.

## **Financing and insurance**

- Does not Apply.
